### Secondary outcomes

The Montreal Cognitive Assessment (MoCA) scale is an assessment tool for rapid screening for mild Cognitive impairment. The Cognitive areas assessed include attention and concentration, executive function, memory, language, visual structural skills, abstract thinking, and computational and directional abilities. The total score of the scale is 30, and the test result shows that the normal value is ≥26.

Patient’s activity of daily living (ADL) is assessed by using the Modified Barthel index (BI), including the patient’s stool, urination, grooming, toileting, eating, transfer, walking, dressing, going up and down stairs, and bathing. A normal score is 100, representing self-care. ADL can be divided into mild (61–99 points), moderate (41–60 points), severe (1–40 points), and completely dependent (0 points).

Quality of Life (QOL) is assessed by using the Short Form 36-Item Health Survey (SF-36), including 8 dimensions: physical functioning, physical and emotional role limitations, bodily pain, social functioning, mental health, vitality, and general health perceptions. SF-36 assesses the quality of life of the disabled older adults, and has proven to have good reliability and validity [26].

The pain Visual Analogue Scale (VAS) is widely used in medicine to measure pain intensity [27]. Draw a 10 cm horizontal line on the paper. One end of the horizontal line is 0, which means no pain; The other end is 10, which means severe pain; The middle section shows different levels of pain. The patient is asked to mark the level of pain on a horizontal line according to how they feel.

fMRI is a non-invasive imaging technique that uses magnetic resonance to measure changes in brain hemodynamics caused by neuronal activity to reflect the activation state of brain regions. The fMRI scans of this study are acquired on a 3-Tesla scanner (SIEMENS VERIO, Erlangen, Germany) in the Yueyang Hospital of Integrated Traditional Chinese Medicine and Western Medicine. In the study, we acquire resting-state fMRI and T1-weighted image scans. Patients will be asked to lay supine in the scanner with their eyes closed but remain awake, and their heads are immobilized with foam pads to minimize head motion. The resting-state fMRI are acquired with the following parameters: repetition time (TR) = 2000 ms, echo time (TE) = 30 ms, flip angle (FA) = 90°, field of view (FOV) = 256 mm*256 mm, matrix = 256*256, slice thickness = 3 mm (no gap) and number of slices = 33. The 3D T1-weighted images are acquired using a brain volume sequence with the following parameters: TR = 1900 ms, TE = 4.6 ms, FA = 9°, FOV = 256 mm*256 mm, matrix = 256*256, slice thickness = 1 mm (no gap) and the number of slices = 160. After data preprocessing, the following indicators can be obtained: Amplitude of Low Frequency Fluctuation (ALFF), regional homogeneity (ReHo), Functional Connectivity (FC), Independent Component Analysis (ICA). ALFF is an effective method to reflect local brain activity by detecting low frequency (0.01–0.1 Hz) fluctuations of the blood oxygen level dependent (BOLD) signal [28]. ReHo reflects the correlation between the time series of a given voxel and that of its neighbors [29]. FC reflects the correlation between different brain regions [30]. ICA is an algorithm of multiple regression analysis, which distinguishes the components of the brain’s resting state network from one of the confounding components [31].

### Safety outcomes

We assess the acceptability and safety of the therapy. Before each patient will be treated, the Internet Addiction (IA) Scale will be used to measure the level of Internet addiction [32]. The Internet Addiction Scale includes: compulsive use, withdrawal, tolerance, time management problems, and interpersonal and health problems. Adverse events such as headaches, dizziness, nausea, vomit, fatigue, or epileptic seizures will be considered safety outcomes. Before and after each treatment, patients will be asked about their physical condition and whether they feel uncomfortable. For each patient, adverse events will be assessed by the simulator sickness question (SSQ) before and after each treatment. The SSQ scale contains 16 items, for example, sweating, nausea, dizziness, burping, headache, blurred vision, and feeling dizzy [33]. Participants will choose “None,” “slight,” “Moderate” or “severe” according to the severity of each item. It is a gold standard for assessing physical illness after exposure to VR environments. Adverse events will be recorded, and severe adverse events will be used as criteria to discontinue the intervention.

An independent safety staff will collect, evaluate, report all adverse events and report directly to the Ethics Committee of Yueyang Hospital of Integrated Traditional Chinese Medicine and Western Medicine.

### Data management

The data will be stored both in hard copy and in digital version as well.

### Statistical analysis

Blind the statistician. The clinical data will be analyzed by SPSS25.0 software. For the measurement data of the obtained data, the normality test is first performed. For the measurement data conforming to the normal distribution, it is expressed as the mean ± standard deviation (x ± s). The paired t test is performed before and after the two groups, and the comparison between the two groups is used Two-way repeated measures analysis of variance (2-way repeated measures ANOVA) test. The non-normally distributed measurement data before and after a group of self-comparison uses the Wilcoxon signed rank test, and comparison between the two groups uses the Mann-Whitney signed rank test. The significance level of the statistical test is set to α = 0.05, and the one-sided test is performed. A data monitoring committee will not be implemented because all participants will be treated and adverse events are expected to be low.

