### Sample size

The sample size was calculated based on the main efficacy indicator (FMA-UE score). We referred to a previous similar study as the basis for estimating the sample size [23]. The means and standard deviations (SDs) of FMA-UE scores in the two groups were 30.41 ± 9.07, 23.00 ± 5.58. The sample size estimation formula is as follows:$$ n=\frac{{\left({Z}_{\upalpha}+{Z}_{\beta}\right)}^2{\sigma}^2}{{\left({u}_r-{u}_c-\varDelta \right)}^2} $$

In this formula, *n* is the required number of each group; Assuming one-sided *α* = 0.025 and one-sided *β* = 0.1; The value of Δ is 10% of the mean of the control group in the previous similar study [24]; The required sample size is 13 in each group; Considering a 20% dropout rate, a total of 32 participants should be recruited (16 per group).

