### Assessment

The study period for each patient is 12 weeks. All patients will be assessed before and after a 4-week intervention for FMA-UE, MoCA, ADL, QOL, VAS, fMRI and safety measures. At week 8 after the end of 4-week intervention, all patients will be assessed their FMA-UE, MoCA, ADL, QOL, and VAS. All outcomes will be measured by assessors who have been uniformly trained, blinded to the randomization group after the baseline visit assessment.

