### Primary outcome

The primary outcome of this study is the mean change in FMA-UE scores between and within the two groups before and after the intervention and follow-up. FMA-UE is widely used in the assessment of upper limb motor function and can reflect the level of upper limb motor function in stroke patients. The total score of the upper limb is 66 points, which is divided into three parts: shoulder–arm (36 points), wrist–hand (24 points), and coordination (6 points), and lower scores indicate worse upper limb movement function. The FMA-UE is often used as the gold standard to test the validity of other scales [9, 25]. FMA-UE has excellent reliability and validity and is sufficiently sensitive to clinical and research practice [20].

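### The planned repeated-measures ANOVA counts baseline FMA-UE as an outcome and leaves the treatment term unnamed; neither candidate term serves the primary comparison as well as a baseline-adjusted model

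*Protocol article*

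**What the plan says.** The Statistical analysis section compares the groups, for normally distributed measurements, as follows: "the comparison between the two groups is used Two-way repeated measures analysis of variance". It adds that "The clinical data will be analyzed by SPSS25.0 software" and that testing is one-sided. It mentions no baseline covariate, does not say whether the group main effect or the group-by-time interaction is the treatment test, and gives no rule for patients with a missing visit.

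The Assessment section fixes three FMA-UE occasions: "All patients will be assessed before and after a 4-week intervention for FMA-UE", and then "At week 8 after the end of 4-week intervention, all patients will be assessed their FMA-UE, MoCA, ADL, QOL, and VAS". The Primary outcome section defines the endpoint as "the mean change in FMA-UE scores between and within the two groups before and after the intervention and follow-up", without singling out one visit. The Sample size section allows for loss: "Considering a 20% dropout rate".

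**The concern.** Taken together, these sections make the pre-treatment score a level of the time factor, hence a response. Randomisation makes the expected group difference zero at that visit. The usefulness of the ANOVA then depends on which term is read as the treatment test.

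- **Group main effect.** This is the literal comparison of the groups. It averages the pre-treatment visit with the two post-treatment visits, so its estimate is not the treatment effect.
- **Group-by-time interaction.** This fits an endpoint defined as change. With three visits, however, it asks only whether the groups' profiles differ in any way. It has no direction and yields no single difference with a confidence interval.

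The plan's own statements pull in opposite directions: a change endpoint points to the interaction, while a one-sided test is possible only for the main effect. At stake are power in a trial of 32 patients and a reportable effect estimate. A further matter is week-4 scores: classical repeated-measures ANOVA uses only patients seen at every visit.

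**Working it through.** **Inputs.** From the Sample size section: "The means and standard deviations (SDs) of FMA-UE scores in the two groups were 30.41 ± 9.07, 23.00 ± 5.58". The difference is 30.41 − 23.00 = 7.41, and the pooled SD is √((9.07² + 5.58²)/2) = 7.53. Also from that section: "Assuming one-sided *α* = 0.025 and one-sided *β* = 0.1", and 13 per group before dropout.

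**The plan's own figure.** (1.960 + 1.282)² = 10.507. Thirteen per group comes out in two ways if Δ is 10% of 23.00, i.e. 2.30 (an assumption):
- two-sample formula with Δ acting as a non-inferiority margin: 2 × 10.507 × 7.53² / 9.71² = 12.64;
- printed formula with the control SD: 10.507 × 5.58² / 5.11² = 12.53.

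Plain superiority without a margin would need 2 × 10.507 × 7.53² / 7.41² = 21.7, i.e. 22. For dropout, 13 × 1.2 = 15.6, i.e. 16 per group. An unadjusted week-4 t test with 13 per group has 67% power, which is the fair reference for what follows.

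**Assumptions not in the documents.** Correlation r between visits (range shown), SD 7.53 at every visit, compound symmetry, an effect of 7.41 at both post-baseline visits, 13 complete patients per group, and two-sided 0.05 (equivalent to one-sided 0.025).

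**Group main effect.** The estimate is (0 + 7.41 + 7.41)/3 = 4.94. Its SE is 7.53 × √[(1 + 2r)/3 × 2/13]. At r = 0.5 this is 2.41, a ratio of 2.05 on 24 df, and power is 50%.

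**Interaction.** The visit differences 0, 7.41, 7.41 deviate from their mean by −4.94, 2.47, 2.47, with sum of squares 36.60. Noncentrality is (13/2) × 36.60 / [7.53² × (1 − r)]. At r = 0.5 this is 8.39 on 2 and 48 df, and power is 71%.

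**Baseline-adjusted.** Residual variance is 7.53² × (1 − r²) for week 4 and 7.53² × [(1 + r)/2 − r²] for the mean of both visits, on 23 df. With complete data these match the mixed-model contrasts. At r = 0.5 power is 77% and 91%.

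| r | Main effect | Interaction | Week-4, adjusted | Mean of both visits, adjusted |
|---|---|---|---|---|
| 0.3 | 59% | 56% | 69% | 88% |
| 0.5 | 50% | 71% | 77% | 91% |
| 0.7 | 44% | 91% | 91% | 97% |
| 0.8 | 41% | 98% | 97% | >99% |

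Simulation with 20,000 trials per setting agrees, and under no effect every test rejects in about 5% of trials. With all 16 per group complete and r = 0.5, the four powers are 60%, 81%, 86% and 96%. Main-effect power falls as r rises because averaging does not use baseline to remove between-patient variation.

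**Incomplete patients.** Twenty per cent of 32 is 6.4, leaving about 26 complete. The plan does not say when patients leave. Without imputation, the number whose week-4 score would go unused therefore lies anywhere between none and about six.

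**The case against.** The case for leaving the plan alone has real substance.

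- **Dilution is not established.** A reader might infer that the planned test certainly shrinks the effect to 4.94. The documents do not support that. The term is unnamed, and an endpoint defined as change fits the interaction, which is not diluted and which removes additive baseline differences. This stands; dilution is conditional.
- **The power gain is not universal.** At r of 0.7 or more the interaction equals or marginally exceeds the week-4 adjusted test. At r = 0, unlikely for one scale in the same patients, even the main effect (79%) beats week-4 adjustment (65%), because it averages two post-treatment visits; the adjusted average reaches 91%. This also stands.
- **Case deletion is not stated.** A reader might infer that the plan discards incomplete patients. It has no such rule; deletion is a property of the classical method and imputation is not ruled out. A missing-data rule may sit in a fuller analysis plan. The inflation for dropout already replaces numbers, though not the unused scores or any bias. A patient lost before week 4 contributes no post-baseline score to the mixed model either.
- **The test is valid.** Type I error is held, so part of this is efficiency.

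What the objection does not answer is that the article itself names the method and the one-sided test. The interaction cannot be one-sided, and the main effect does not estimate the stated endpoint.

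**Conclusion.** The point holds in conditional form. Baseline FMA-UE is, by implication, a repeated outcome, the treatment term is not fixed, and each candidate has a defect. The main effect estimates two thirds of a constant effect, with power of about 59% to 41% over r = 0.3 to 0.8. The interaction has power of about 56% to 98% but neither direction nor a single estimate. A baseline-adjusted model avoids both defects. Its week-4 contrast gains about 14 points over the interaction at r = 0.3 and 6 at r = 0.5, and nothing from 0.7 upward; the average contrast is the most powerful in the table throughout.

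These sizes rest on the assumed correlations, equal SDs, compound symmetry and a sustained effect. It would be wrong to blame the ANOVA for the whole distance from the planned 90%, since an unadjusted week-4 comparison has only 67% at 13 per group. The one-sided 0.05 in the Statistical analysis section also differs from the one-sided 0.025 used here and in the Sample size section, which is a separate matter.

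**What to change.** For FMA-UE, replace the ANOVA with a linear mixed model (SPSS MIXED). Week 4 and the follow-up visit are the responses, baseline FMA-UE is a covariate, and group, visit and group-by-visit are fixed effects with unstructured covariance. Include every randomised patient with any post-baseline score; this keeps a patient who has week 4 but misses follow-up.

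Name one primary contrast before unblinding, reported with its confidence interval:
- **Average over both post-baseline visits:** closer to the Primary outcome section, with about 88% to almost 100% power if the effect is sustained.
- **Week-4 difference:** simpler, and unaffected by a fading effect. If the effect halves by follow-up, the average contrast has about 66%, 71%, 84% and 93% power at r = 0.3, 0.5, 0.7 and 0.8, against about 70%, 78%, 91% and 98% for week 4.

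The cost is one error degree of freedom (24 to 23 with 13 per group) and the need to fix a primary contrast that the protocol leaves open. That choice sharpens the endpoint, so it is more than a wording change and should be recorded as such. No extra patients, visits or software are needed. The separate non-parametric route for non-normal data is not covered by this change.

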## Methods and design

### Study design

This is a single-center, assessor-blinded, randomized controlled clinical trial. This trial was approved by the Ethics Committee of Yueyang Hospital of Integrated Traditional Chinese Medicine and Western Medicine. In this trial, a randomized controlled study will be used, and all eligible patients will be randomly divided into 2 groups according to the ratio of 1:1, namely VRMT group and RAVRMT group. There will be a 4-week intervention and a 12-week follow-up. Outcome measurements include the Fugl-Meyer motor function assessment -Upper Extremity (FMA-UE), fMRI, and others. The flowchart of this trial is shown in Fig. 1.

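### The one-sided rule is undefined for the group-by-time F test of the planned repeated-measures ANOVA, so the between-group decision on FMA-UE needs one named, signed contrast

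*Protocol article*

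**What the plan says.** The Primary outcome section defines the endpoint as "the mean change in FMA-UE scores between and within the two groups before and after the intervention and follow-up". There are two arms (Study design). The Assessment section places FMA-UE before treatment and after the 4 weeks, and adds a third visit: "At week 8 after the end of 4-week intervention, all patients will be assessed their FMA-UE, MoCA, ADL, QOL, and VAS".

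The Statistical analysis section names these tests:
- Between groups, normal data: "the comparison between the two groups is used Two-way repeated measures analysis of variance (2-way repeated measures ANOVA) test".
- Within groups, normal data: "The paired t test is performed before and after the two groups".
- Between groups, non-normal data: "comparison between the two groups uses the Mann-Whitney signed rank test".

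One rule then covers them all: "The significance level of the statistical test is set to α = 0.05, and the one-sided test is performed". The section does not say which ANOVA effect decides, which contrast supplies the direction, or how a one-sided p value is to be obtained from an F statistic. It does not mention halving a p value.

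**The concern.** A one-sided test needs a statistic with a sign. The paired t, Wilcoxon and Mann-Whitney tests have one. A 2-df interaction F does not: it rejects for any difference in pattern over the three visits, including one in which RAVRMT does worse. The trial's question is whether RAVRMT improves function more than VRMT, which is directional. For normally distributed FMA-UE data, the stated rule and the stated test therefore do not fit together.

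Two things are at stake. First, analysts following the same sentence could reach different significance statements from the same data. Second, whether the between-group decision has a direction at all depends on the result of the preliminary normality test, because the non-normal branch can be run one-sided and the interaction F cannot.

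**Working it through.** **Inputs.** Two arms and three FMA-UE visits (Study design, Assessment). Means 30.41 and 23.00, SDs 9.07 and 5.58, 13 per group before dropout and 16 after (Sample size). The difference is 30.41 − 23.00 = 7.41. The pooled SD is √[(9.07² + 5.58²)/2] = √56.70 = 7.53. Assumed, because the document gives no value: normal data, compound symmetry, and within-patient correlation between 0.5 and 0.85.

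**The plan's own figure.** Thirteen per group is reproduced by 2(1.960 + 1.282)² × 56.70 / (7.41 + 2.30)² = 12.64, rounded up to 13. This takes Δ = 2.30, which is 10% of 23.00, as a margin added to the difference. The formula as printed has no factor 2 and subtracts Δ, and gives 22.8. That is a separate matter. Here 13 and 16 serve only as group sizes, and 13 × 1.2 = 15.6 gives the 16.

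**Step 1: degrees of freedom.** The interaction null states two equalities: no between-group difference in change from baseline to week 4, and none in change from baseline to the follow-up visit. Hence (2 − 1)(3 − 1) = 2 numerator df. With 13 per group the denominator has 2 × (26 − 2) = 48. The two differences can have opposite signs, so the F statistic has no sign to test.

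**Step 2: null rejection rate of each possible reading.** Simulated null trials (50,000 per setting, 13 or 16 per group, correlation 0.5 or 0.8):

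| What the analyst does with the interaction F | Null rejection rate |
|---|---|
| Uses p < 0.05 as printed | 4.8–5.0% |
| Halves p, ignores direction | 9.8–9.9% |
| Halves p, week-4 change must favour RAVRMT | 4.9–5.1% |
| Halves p, both later changes must favour RAVRMT | 3.3–3.4% |
| Halves p, either later change may favour RAVRMT | 6.6–6.7% |

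The second row is arithmetic: p/2 < 0.05 is p < 0.10, which occurs in 10% of null trials. The third row is half of that, by symmetry.

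**Step 3: behaviour under a true effect.** With 13 per group and an effect of 7.41 at both post-baseline visits, the F test as printed gives p < 0.05 in 71% of trials at correlation 0.5 and 91% at 0.7. The percentages are the same for −7.41.

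**Step 4: the group main effect.** This has 1 df, so F = t² and it can be signed. Halving its p with a direction check gives 4.9–5.1% under the null. But it averages all three visits, including baseline. An effect of 7.41 present only after baseline becomes (0 + 7.41 + 7.41)/3 = 4.94, two thirds of its size. One-sided power at 0.05 with 13 per group and correlation 0.5 to 0.85 is 53–64%. For the between-group difference in week-4 change it is 79–99.7%.

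**Step 5: a signed contrast.** Let D be the RAVRMT mean change minus the VRMT mean change at one visit. Then t = D / √(2s²/n) on 2n − 2 df, where s is the SD of the change. Run one-sided on the week-4 change, its null rejection rate is 4.9–5.1% at 0.05 and 2.4–2.6% at 0.025.

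**The case against.** A reader might infer that the between-group analysis cannot be carried out at all, and that the plan has a 10% false-positive rate. The document supports neither.

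- The section does not say that the interaction decides. The group main effect has 1 df and can be signed, as can any single contrast from the same model, and the other named tests can all be run one-sided.
- The 10% requires an analyst to halve p and then ignore which arm did better. The protocol does not tell anyone to halve p, and ignoring direction would itself breach a one-sided rule. With the check that one-sided implies, on the week-4 change, the rate is about 5%, the level stated.
- Used as printed, the F test does not inflate error. By symmetry about 2.5% of null trials reject with the week-4 change favouring RAVRMT. That it also rejects for harm is true of every non-directional test, and the reported means would show the direction.
- Which effect or contrast decides is often left to an analysis plan, and none is shown here.

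The first three points stand and limit the claim. The first does not remove the problem: the primary outcome is a change, and the group main effect does not test change. The fourth does not answer it either. The document does more than leave a detail open. It states a test and a rule that do not fit together for its primary outcome, and a later analysis plan can repair that only by departing from one of them or by adding a contrast this document does not name.

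**Conclusion.** The point holds in limited form and should be corrected. For normally distributed FMA-UE data, the one-sided rule is undefined for the term that compares change between arms. As printed, that F test is a sound non-directional 5% test, but it is not the one-sided test the section promises. Attempts to make it one-sided give about 3% to 10% under the null, and 10% is the extreme case, in which direction is ignored.

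These figures assume normality, compound symmetry, correlations of 0.5 to 0.85 and 13 or 16 per group. The 2 df and the absence of direction depend on none of these, only on two arms and three visits.

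The Sample size section uses one-sided α = 0.025 and the Statistical analysis section one-sided 0.05. That mismatch is a separate issue and is not needed for this conclusion.

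**What to change.** In the Statistical analysis section, state that the between-group decision rests on one signed 1-df contrast: the RAVRMT minus VRMT difference in FMA-UE change from baseline at one named visit. It is tested by its t statistic and reported with a confidence interval. Add that the ANOVA F tests are supportive and non-directional, and that their p values are not halved. Choose the level of the contrast so that it agrees with the level used for sizing.

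The cost is two or three sentences. The contrast uses FMA-UE scores already scheduled and the same software, with no new visits, patients or data. The wording should be settled before anyone sees outcomes by arm.

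### The trial is sized at one-sided α = 0.025 but its analysis rule is one-sided α = 0.05, and the named ANOVA F test has no direction

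*Protocol article*

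**What the plan says.** The Sample size section of the protocol article sets the error rates for planning: "Assuming one-sided *α* = 0.025 and one-sided *β* = 0.1". On that basis it reports: "The required sample size is 13 in each group". An allowance for 20% dropout raises this to 16 per group, 32 in total.

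The Statistical analysis section sets the rule for judging results: "The significance level of the statistical test is set to α = 0.05, and the one-sided test is performed". For normally distributed data, "the comparison between the two groups is used Two-way repeated measures analysis of variance (2-way repeated measures ANOVA) test". For other data, "comparison between the two groups uses the Mann-Whitney signed rank test".

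The Assessment section schedules FMA-UE three times: before the intervention, after its 4 weeks, and 8 weeks later. The Primary outcome section defines the outcome as mean change in FMA-UE. The Statistical analysis section does not say which assessments enter the ANOVA.

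**The concern.** The two sections use different significance levels for the same kind of test. One-sided 0.025 corresponds to the usual two-sided 0.05. One-sided 0.05 corresponds to two-sided 0.10 and is the looser rule. Had the analysis section said two-sided 0.05, the sections would agree, but it says one-sided.

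The analysis section also conflicts with itself. It prescribes one-sided testing, yet its between-group method for normal data is an F test, which rejects for differences in either direction. An analyst cannot follow both statements without a choice that the article does not record.

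At stake is the chance of declaring RAVRMT better than VRMT when it is not. As written, that chance can be 2.5% or 5%, depending on which branch the normality test selects and on how the analyst interprets one-sided for an F test.

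**Working it through.** **Inputs from the Sample size section.** "The means and standard deviations (SDs) of FMA-UE scores in the two groups were 30.41 ± 9.07, 23.00 ± 5.58", a difference of 30.41 − 23.00 = 7.41. "The value of Δ is 10% of the mean of the control group in the previous similar study", so Δ = 0.10 × 23.00 = 2.30 and u_r − u_c − Δ = 5.11. One-sided α = 0.025, β = 0.1.

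**1. Reproducing the plan's figure.** The printed formula is n = (Zα + Zβ)²σ² / (u_r − u_c − Δ)². The article does not say which σ was used. With σ = 5.58:

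- at one-sided 0.025: (1.960 + 1.282)² × 5.58² / 5.11² = 12.53, rounded up to 13, the stated figure;
- at one-sided 0.05: (1.645 + 1.282)² × 5.58² / 5.11² = 10.21, rounded up to 11.

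For dropout, 13 × 1.2 = 15.6, so 16 per group and 32 in total, as stated. The same step from 11 gives 13.2, so 14 per group and 28 in total. With the formula and Δ as printed, one-sided 0.05 does not give 13 at σ = 5.58, 7.53 (defined in step 4) or 9.07 (10.21, 18.60 and 26.98). Only by dropping Δ and using σ = 9.07 does 0.05 give 12.83, and that departs from the printed formula. The stated size therefore fits the stated 0.025. This is a check on the α level only, not on the choice of σ or the form of the formula.

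**2. Directional test at each level.** Under the null hypothesis the favourable-direction error is α itself: 0.05 against 0.025, a ratio of 2. With 16 per group (30 df) the critical t is 1.697 against 2.042. A simulation of 200,000 null trials with 16 per group gave 0.0494 and 0.0245.

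**3. The named F test at 0.05.** The 5% critical value of F(1,30) is 4.171 = 2.042², so a 1-df F test is the two-sided 0.05 t test. In the same simulation it rejected in 0.0494 of trials overall and in 0.0245 with the difference favouring RAVRMT. To match one-sided 0.05, the F test would have to be run at 0.10: F(1,30) = 2.881 = 1.697².

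If all three FMA-UE assessments enter the model, the group-by-time interaction has (2 − 1) × (3 − 1) = 2 numerator df. With 32 complete patients the critical value is F(2,60) = 3.15. This statistic has no sign, so halving its p-value has no meaning.

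**4. Illustration on the score scale.** The assumptions are a two-sample t test on raw FMA-UE scores, 13 per group (24 df) and no margin. The critical difference is t × SD × √(2/13). One assumed SD is √((9.07² + 5.58²)/2) = 7.53, the other is 5.58.

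| Assumed SD | One-sided 0.05 (t = 1.711) | One-sided 0.025 (t = 2.064) |
|---|---|---|
| 7.53 | 5.05 | 6.10 |
| 5.58 | 3.74 | 4.52 |

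**The case against.** The strongest objection is that the 0.025 governs sizing only, that just one section sets an analysis threshold, and that the named ANOVA at 0.05 already delivers about 2.5% in the favourable direction for a 1-df effect. On that view nothing is inflated. The arithmetic is right, and it limits the point: a reader might infer that the false-positive rate is doubled whatever is done, and the article does not support that. Doubling requires that a directional test at 0.05 is actually run. But this defence works only by ignoring the explicit one-sided instruction, and it does not cover the Mann-Whitney branch, which can be run one-sided at 0.05 exactly as written.

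It can also be said that model detail belongs in an analysis plan that is not shown, and that an ANOVA on the before and after values alone would have a 1-df interaction that can be recast as a signed contrast. Both are fair. The 2-df difficulty is conditional on all three assessments being used. The conflict between the two stated α levels is not.

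Two further inferences should be resisted. One is that worsening on a secondary outcome such as VAS-pain could never reach significance. The article gives no direction for the one-sided test on any outcome, and an F test would detect a difference either way. The other is that 5.1 and 6.1 points are this trial's decision thresholds. They rest on an assumed SD, on raw scores although the outcome is change (for which no SD is given), and on no margin. With the smaller SD the whole window moves to about 3.7 to 4.5, and testing against Δ would add 2.30 to every figure.

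**Conclusion.** The point holds as a contradiction in the article's current text. Planning uses one-sided 0.025, the analysis rule is one-sided 0.05, and the article does not reconcile them. The size is conditional: 5% instead of 2.5% in favour of RAVRMT if a directional test is run at 0.05, and about 2.5% if a 1-df ANOVA F test is run at 0.05, in which case the one-sided statement is not being followed. A 2-df interaction over three assessments cannot be tested one-sided at all. These are alternative consequences and do not occur together for the same test.

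The error rates follow from the stated levels and do not depend on the SD. The score differences in the illustration do depend on it and serve only to show that results of plausible size could change status: a gap of about 0.8 to 1.0 points between the two rules under the stated assumptions.

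**What to change.** In the Statistical analysis section, replace the statement of one-sided testing at 0.05 with: *two-sided α = 0.05 (equivalent to the one-sided 0.025 used for the sample size)*. Stating one-sided 0.025 would reconcile the levels equally well, but the two-sided wording also fits the F test.

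Then test the primary between-group question with one prespecified single-df contrast at a named time point, for example the group difference in FMA-UE change from baseline to the end of the 4-week intervention. The repeated-measures ANOVA can remain as a supporting analysis. With only the before and after values in the model, its interaction is the same test as this contrast.

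The planned 13 per group and 32 in total stay as they are. The cost is a short edit and a stricter nominal threshold, equal to the one used for planning.
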